**STATISITICAL ANALYSIS**

- All data will be collected together to the person who is in charge of data collection. The data will be save as Excel file format.
- When the study is finished, we will discuss with statistician from the host university in managing and analyze the data.
- The data will be presented as mean±SE and SPSS18.0 (SPSS inc., Chicago, USA) will be used for the analysis. Baseline characteristics and safety outcomes will be compared between the TDF treatment and the controls using t-tests for continuous variables and chi-square tests or fisher exact tests for categorical variables. The Mother-to-child transmission rate and the recovery levels of the HBV DNA 28 weeks after the delivery between the two groups will be compared by Fisher exact tests. A mixed model, repeated measures analysis for variance will be used to analyze if the serum HBV DNA levels change differently with or without TDF treatment. The planned contrasts will be tested for the "change in HBV DNA for each group between baseline and delivery time" and "differences from weeks to the weeks’ within TDF treatment group. The p value less than 0.05 will be considered as statistically significant.
- All data will be confidential during and after the study. The data will be transferred and stored in the server of the hospital. Special authorization is needed to access these data after the closure of the study.

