**HYPOTHESIS**

Based on the evidences described above, the TDF effectively inhibits the HBV replication with less renal toxicity. Particularly, it is also effective in the patients tolerating to other NAs treatment and no drug resistance is reported. Intriguingly, the TDF has been tested in the pregnancies at the late stage of gestation against HBV infection. However, the prospective studies with large sample size and control populations are lacked to confirm definitely the safety and efficacy of TDF on the pregnant women and infants.

Therefore, the present trial is designed to prospectively investigate the effect of TDF in the pregnancies. The pregnant women will be randomly grouped into TDF treatment and control subjects. To test its maximal effect, the patients who are HBsAg/HBeAg positive with high viral burdens will be selected, since, as mentioned above, the HBxAg and HBV DNA levels are closely associated with intrauterine HBV infection. On the other hand, the application of TDF at late stage of the gestation might be too late to block intrauterine HBV infection, particularly, in the pregnancies who are HBsAg/HBeAg-positive with high viral burdens. Thus, we propose to give TDF treatment at the mid stage of gestation (24 weeks) to inhibit the intrauterine infection by HBV.

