**STUDY OBJECTIVES**

The present prospective study aims at investigating the effect of TDF against the mother-to-child transmission of HBV infection. Through this trial, we will:

(1) confirm the efficacy of TDF in blocking HBV intrauterine infection during pregnancy;

(2) monitor the effect of TDF on the dynamic changes of HBV DNA levels in the pregnancy;

(3) test the HBsAg and HBeAg expression during and after the TDF treatment;

(4) screen the changes of HBV resistance genes related to the NAs treatment in the pregnant women with chronic HBV infection;

(5) clarify the adverse effects induced by TDF treatment during the pregnancy for both mother and infants.

This clinical project will allow us to better understand the safety and efficacy of TDF against HBV infection during the pregnancy. It will also help in clarifying the potential adverse effects of this medicine. The study will also provide the evidence to further optimize and to facilitate the TDF application in blocking the vertical transmission of HBV infection.

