**STUDY DESIGN**

A random study will be designed to investigate the effect of TDF in blocking vertical transmission of the HBV infection.

Before starting the trial, we estimate the sample size using online sample size calculator for two parallel-sample proportions (http://clincalc.com/stats/samplesize.aspx). According to the literatures, we learn that after routine immunoprophylaxis the mother-to-child transmission of HBV infection is around 10-30% (we proposed as 30% for the calculation). We expect the TDF treatment will reduce the infection to 5-10% (we perform calculation as 5%). The superiority margin is supposed to be 0.05. So, we have an estimated samples size with equal allocation as 35 for each group. The present trial will collect 60-80 individuals for each group.

We will randomly allocate patient number into TDF and control group based on the random number table. The patients for the study will be selected as shown in the bellowing flow chart. When the pregnant women visit the hospital for the first time, generally, the routine care will be given and the laboratory parameters of blood sample including blood cell counts, HBV parameters, liver function, kidney function, etc. will be checked. The ultrasound of foetus will also be performed. Based on the laboratory data and history, the non-eligible pregnancies will be excluded. The eligible pregnant women will be further selected according to the criteria. Then, the final enrolled pregnancy will be numbered as the visiting order. This patient number will be corresponded to the allocated number from random number table.

During the study, the patient will be excluded if special situation occurs including preterm delivery, lost follow up or any other severe side effects.

[figure not shown]

- Subject:

According to our experiences, it is estimated that around 80-150 pregnancies with HBV infection will visit our hospitals. Three hundred to 500 HBV-infected pregnant women totally will be predicted in 3-4 years.

- Eligibility criteria

20-35 years old pregnant women with the HBV infection.

- Inclusion criteria

The pregnancies who are HBeAg/HBsAg double positive as well as serum HBV DNA≥2×106 (6.3 log10) IU/mL.

- Exclusion criteria

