① co-infection with HIV, HCV or HDV; ② HBV treatment history within 6 months; ➂ abortion history or clinical manifestation of inevitable abortion; ④ congenital deformity of foetus; ⑤ hepatocellular carcinoma evidence, renal or hepatic dysfunction, creatinine clearance rate <100mL/min, alanine aminotransferase (ALT) >5 times of upper limit of the normal level, bilirubin >2mg/dl; ⑥haemoglobin <8g/100mL, neutrophil <1000/mm^3^, albumin <2.5g/100mL; ⑥ special medicine treatment during the pregnancy; ⑦ biological father of infant has chronic HBV infection.

- Randomization

Based on our prediction, less than 50 pregnancies per year are eligible for the study. To ensure the similar number for treatment and control group, we estimate that minimal 30 subjects can participate in the study (total around 120 subjects). When getting 120 subjects, the enrolment will be stopped.

In random number table, we randomly start and separate 3 digital number as group following the order in number table. The separated number are written on the paper following the order of the random number table. The repeated number and number big than 120 will be excluded. The first 60 number based on the order will be allocated as TDF treatment. The left will be controls.

- Conceal the intervention

The selected number and corresponding intervention will be hided in the individual envelope and sealed. On the surface of the envelop, the selected number is written. Then the envelops are managed in order (from 001 to 120) and given to the doctor when having the enrolled subject (visiting order).

- Ethics

We have got the approval from the hospital for the study (approval N° 2012-136). The consent will be prepared and printed. The patients will be informed and sign the written consent.

- Potential benefit to the subjects

The TDF therapy in the HBV-infected pregnant women with high viral loads will help in reducing the risk of mother-to-child transmission. It will also protect mothers during the gestation periods due to the special immune situation. In addition, it will help to understand the safety and efficacy of TDF in blocking the vertical transmission, its effect on mothers and infants and potential adverse effects, which will facilitate the TDF treatment in the pregnancies in clinic.

- Potential risk

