The most potential risk for the trial is the side effects of TDF, such as preterm delivery and severe adverse effects including dysfunction of liver and kidney as well as the HBV resistance to TDF treatment. The trial has no apparent physical, psychological and economic effect. The pregnancies will not have any stress or discomfort when answering the question or focusing on the research. The participants will face the same stress as other pregnancies when collecting blood routinely.

- Methods to protect the privacy, data and right of subjects

Before starting the trial, the participants will be informed, agree and sign the printed consent. All the personal information will be confidential. A person will specifically manage the collected data that will be saved in the computer with password. Only this person can access the computer.

- Intervention

The TDF therapy will be given to the pregnant women who are HBsAg/HBeAg-positive with high viral burdens. The details of the medicine will be concealed. The pregnancies will take the medicine orally, 300mg/day, starting the date of enrolment (24 weeks of gestation) until 4 weeks postpartum. This dose is recommended by the manufacture and also used by most of the studies. The method used for assigning subjects to the treatment group is described above in the section of randomization.

The medicine will be distributed to the participants every time when visiting the doctor. The medicine will be prepared and packaged in the pharmacy centre of the hospitals.

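### Safety outcomes are compared only by p<0.05 tests of no difference, which at this trial's size cannot support a safety conclusion for uncommon harms

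*Protocol*

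**What the plan says.** On safety, the Statistical Analysis section of the protocol states: "Baseline characteristics and safety outcomes will be compared between the TDF treatment and the controls using t-tests for continuous variables and chi-square tests". For categorical outcomes the full choice is "chi-square tests or fisher exact tests for categorical variables". One threshold covers all analyses: "The p value less than 0.05 will be considered as statistically significant". Data are to be shown as mean ± SE, and no other basis for judging a safety difference is given.

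Other sections bear on this:

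- **Study Objectives**, item 5, is to "clarify the adverse effects induced by TDF treatment during the pregnancy for both mother and infants".
- **Hypothesis** says that large controlled studies are lacking "to confirm definitely the safety and efficacy of TDF on the pregnant women and infants", and then introduces this trial.
- **Study Design** derives 35 per group from transmission of 30% against 5%, then says "The present trial will collect 60-80 individuals for each group". Under Randomization it says "When getting 120 subjects, the enrolment will be stopped", with 60 numbers going to TDF and the rest to control.
- **Potential risk** names the harms of interest: "side effects of TDF, such as preterm delivery and severe adverse effects including dysfunction of liver and kidney".
- **Study Design** also says that a woman is excluded during the study if she delivers preterm, is lost to follow-up or has another severe side effect.

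**The concern.** A test of no difference answers one question: are the data incompatible with equal risk? If p is above 0.05, the test alone does not say how large an excess is still possible. The sample size was chosen to find a 25-point difference in transmission. The harms that the protocol names may be much less frequent than that, and an important excess may be much smaller than 25 points. For such harms a non-significant result is likely whether or not TDF causes them.

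What is at stake is the safety statement for use in pregnancy. If the report gives only p values, a reader cannot tell a harm that has been ruled out from one that the trial was too small to see. Any mistake here runs in the unsafe direction, because rarer harms and fewer women both make a non-significant result more likely.

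**Working it through.** **1. The protocol's own figure.** Inputs from Study Design: p1 = 0.30, p2 = 0.05, equal allocation. Assumed: two-sided alpha 0.05 and 80% power, since neither sidedness nor power is stated. With mean proportion 0.175:

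n = [1.960 × √(2 × 0.175 × 0.825) + 0.842 × √(0.30 × 0.70 + 0.05 × 0.95)]² / 0.25² = (1.053 + 0.427)² / 0.0625 = 35.1

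This is 36 rounded up, and power at 35 per group is 79.9%. The stated 35 is therefore reproduced. No safety outcome enters it.

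**2. Chance that the planned tests miss a doubling.** The protocol gives no adverse event rates, so control rates from 5% to 20% are assumed. The method is exact enumeration of two independent binomials with n women each. The probabilities of all tables with two-sided p<0.05 are summed, and the miss rate is one minus that sum. Chi-square is without continuity correction.

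| Control v TDF rate | 60 per arm, Fisher / chi-square missed | 80 per arm, Fisher / chi-square missed |
|---|---|---|
| 5% v 10% | 91% / 83% | 86% / 79% |
| 10% v 20% | 75% / 67% | 65% / 58% |
| 15% v 30% | 58% / 49% | 44% / 37% |
| 20% v 40% | 40% / 32% | 26% / 20% |

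The 60 follows the stop at 120 in all, and the 80 is the upper end of the 60-80 per group. These two statements conflict, but for control rates up to 10% the conclusion is the same at either size.

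**3. What an interval would add.** Newcombe's 95% interval for a risk difference combines the Wilson limits (l, u) of the two proportions. Its upper limit is d + √[(u1 − p1)² + (p2 − l2)²].

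- Equal counts, 6/60 v 6/60: the Wilson limits for 10% are 0.0466 and 0.2015. The upper limit is 0 + √(0.1015² + 0.0534²) = 0.115. The estimate is no difference, yet an excess of about 11 points is not excluded.
- 9/60 on TDF v 3/60 on control: d = 0.10. Fisher p = 0.125. Chi-square z = 0.10 / √(0.10 × 0.90 × 2/60) = 1.83, p = 0.068. Both are non-significant, while the interval runs from −1.1 to +21.6 points.

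In both cases the p value says only that the result is not significant. The interval shows how much harm remains possible.

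**4. The population compared.** The Statistical Analysis section compares safety outcomes between TDF and control. Study Design excludes women who deliver preterm or have severe side effects. Preterm delivery and severe adverse effects are also the harms named under Potential risk. Read together, the events of most interest could leave the comparison before any test or interval is calculated.

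**The case against.** The strongest reply is that the protocol claims nothing improper. It says that safety outcomes will be compared, and nowhere says that p>0.05 establishes safety. A reader might infer such a rule from the single p<0.05 criterion together with the Hypothesis section, but the text does not support this. The phrase about confirming safety definitely describes a gap in earlier studies. The trial's own stated purposes are to investigate, evaluate and clarify. This part of the reply stands, so the Hypothesis and Objectives sections need no rewording.

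It can also be said that sizing a trial on its primary outcome is ordinary, that low power for uncommon harms is common at this size, and that interval reporting or a harm margin may be left to a statistical analysis plan. All of this is fair. Neither low power as such nor the lack of a margin is an error here. What remains is that the protocol does fix a method for safety, and that method is ill suited to its fifth objective.

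A further stronger reading is that any doubling of harm would usually be missed. That is not so without a condition on the control rate. At 60 per arm a doubling from 15% is about even, and from 20% it is detected 60% (Fisher) to 68% (chi-square) of the time. For a continuous safety value, a difference of 0.5 SD is missed by the t-test only about 22% of the time. Nor does every suggestive split go undetected: 10 v 3 events gives Fisher p = 0.075 but chi-square p = 0.040, and the protocol allows either test.

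**Conclusion.** The point holds in a limited form. The protocol judges safety only by tests of no difference at p<0.05, in a trial sized for a 25-point difference in transmission. A non-significant result could not support a safety conclusion for harms with control rates up to about 10%. At 60 per arm, 67% to 91% of true doublings would be missed, depending on the test and on whether the control rate is 10% or 5%. At 80 per arm the range is 58% to 86%.

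These figures rest on assumed control rates, two-sided testing and complete data in both arms. They do not extend to harms with control rates of 15% to 20% or more. They also do not show that the investigators intend to read a null result as safe. The exclusion of women with preterm delivery or severe side effects is a separate conflict with the safety comparison, and interval estimates alone would not repair it.

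**What to change.** In the Statistical Analysis section, replace the bare p-value comparison of safety outcomes with estimation:

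- For each harm named under Potential risk, report the risk difference between arms with a 95% confidence interval (Newcombe, for example). For continuous safety values, report the mean difference with a 95% confidence interval. Include all randomised women, in the arm to which they were allocated.
- Add wording such as: A p value above 0.05 will not be taken as evidence of safety; the conclusion for each harm will give the largest excess risk that the 95% interval does not exclude.
- Reconcile the exclusion rule in Study Design with the safety comparison, so that preterm deliveries and severe side effects are counted as events in the analysis. This concerns who is analysed, not the clinical management of these women.
- Reconcile 60-80 per group with the stop at 120, so that the available precision can be stated.

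The cost is small: a few sentences and intervals from data already planned. The estimates themselves need no extra women or visits. The downside is a more modest safety statement.

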**Abstract*:**

After more than 20 years of studies on the mother-to-child transmission and the therapy strategies against hepatitis B virus (HBV) infection, we have known that the HBsAg/HBeAg and HBV DNA level are the predominant factors related to the HBV intrauterine infection. The present project will prospectively investigate the effect of tenofovir disoproxil fumarate (TDF), a nucleotide analogue against viral infection, in blocking the HBV vertical transmission and the potential mechanism involved in this process among the pregnant women who are HBsAg/HBeAg-positive with high viral loads. The trial will be randomly designed. We will check the efficacy and rationality of the TDF in blocking the mother-to-child transmission of HBV infection (primary outcome). We will dynamically monitor the HBsAg/HBeAg, HBV DNA levels (secondary outcome) and liver function of the women during the pregnancy and the hepatitis B parameters, HBV DNA level (secondary outcome) and liver function of infants immediately after the birth and at age of 7 months. The ratio of T lymphocytes and cytokines level in the serum related to the HBV infection will also be checked (before TDF intervention, before and after delivery, etc) to reveal the effect of TDF on the immune function of the pregnancies, which will help to determine whether the changes of immune system by TDF contribute to the block of vertical transmission of HBV. The known and/or potential mutation site(s) of genes related to the drug resistance or tolerance will be examine by PCR in the pregnancies after TDF treatment, which will facilitate the subsequent therapy against chronic HBV infection. The infants from TDF treated mothers will be followed up till 2 years old and monitor the growth curve and IQ value. In summary, the present study will allow us to evaluate the efficacy and safety of TDF in the pregnancies and to provide the evidence of TDF against HBV during the pregnancy.

*** Since the original protocol was wrote in Chinese and there are too much contents, I try my best to translate the key points of the protocol into English.**

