**STUDY PROCEDURES**

- Screening for eligibility

The participants will be screened by the consulting doctor when they visit the hospital for the first time based on the criteria. The potential eligible pregnancies will be monitored every 4 weeks till 24 weeks of gestation. According to the parameters of pregnancies at 24 weeks of gestation, the pregnant women will be enrolled or not for the study.

- Visit

The enrolled pregnant women will visit the doctor every 4 weeks till 28 weeks postpartum.

- Data collection

Routinely, when patients visit doctor for the first time, all personal information will be recorded as electronic file including birth date, home address, contact information, family condition (family members, estimated annual income, work condition, etc), health history, etc. The medical records from other hospital(s) will also be collected.

The consulting doctor will provide the prescription for the lab examination or other examination such as ultrasound and infant monitor. All the obtained results from the examination will send back to the doctor. The person who is charge of the study will record all data in the specialized computer.

- Outcomes measurement

The primary outcome is the mother-to-child transmission of HBV infection, which will be determined when the infant’s serum HBV DNA is higher than 20 IU/ml or HBsAg is positive 28 weeks after the birth.

The secondary outcome is the recovery of HBV DNA levels at 28 weeks postpartum in the pregnancies with or without TDF treatment after the cessation of TDF treatment.

- Safety and adverse event monitoring

The doctor will carefully ask the condition and situation of the pregnancies during the consultation. At the same time, the safety is also monitored by the blood assay.

Based on the severity of patients’ situation (vomit, rash on the skin, liver and kidney function, etc), the doctor will give the corresponding treatment and decide whether withdrawing the study for the patient.

The emergence contact information will be provided to the pregnancies in case needing help and suggestion from doctor as well as reporting the adverse events. All the adverse effect will be recorded till the complement of the follow-up.

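### The secondary outcome, recovery of maternal HBV DNA at 28 weeks postpartum, is given Fisher's exact test without a category to count or a meaning of recovery in controls

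*Protocol*

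**What the plan says.** The Outcomes measurement item under Study Procedures states: "The secondary outcome is the recovery of HBV DNA levels at 28 weeks postpartum in the pregnancies with or without TDF treatment", and completes the sentence with "after the cessation of TDF treatment". The Statistical Analysis section puts this outcome in one sentence with the transmission rate and says that "the recovery levels of the HBV DNA 28 weeks after the delivery between the two groups will be compared by Fisher exact tests". Just before that, for baseline and safety data, the same section assigns t-tests to continuous variables and chi-square or Fisher tests to categorical ones.

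The section also plans a mixed model for serum HBV DNA over time. It names two sets of contrasts: change from baseline to delivery in each group, and differences between weeks within the TDF group.

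On the arms, the Hypothesis section says "The pregnant women will be randomly grouped into TDF treatment and control subjects". The Intervention item under Study Design gives the TDF period as "starting the date of enrolment (24 weeks of gestation) until 4 weeks postpartum".

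The Abstract attaches the secondary-outcome label elsewhere: "We will dynamically monitor the HBsAg/HBeAg, HBV DNA levels (secondary outcome) and liver function of the women during the pregnancy", and, for the infants, "HBV DNA level (secondary outcome) and liver function of infants immediately after the birth and at age of 7 months".

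**The concern.** A viral level is a measurement, and Fisher's test needs a table of counts. To apply one to the other, someone must first decide which women have recovered, and the protocol does not say how. The gap is wider in the control arm, because recovery is defined by an event, stopping TDF, that does not happen there.

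Two things are at stake. First, the result may depend on a cut-point chosen late: the Statistical Analysis section says that the statistician will be consulted once the study is finished. Second, turning the level into a yes/no variable discards information that the scheduled blood samples already provide.

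**Working it through.** **Does the plan define what Fisher's test would count?** For the primary outcome it does: an infant counts as infected if HBV DNA exceeds 20 IU/ml or HBsAg is positive at 28 weeks. That is binary, and Fisher's test fits. For maternal recovery, neither the outcomes item nor the analysis section gives a threshold, a reference value or a scale.

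**Is recovery meaningful in both arms?** TDF stops 4 weeks postpartum, so treated women have been off the drug for 28 − 4 = 24 weeks at the 28-week visit. Controls have no such interval. Three readings are possible, and each treats controls differently:
- Return to the 24-week gestation value: controls had no TDF-induced fall to return from.
- Rise from the delivery value: the rise after stopping TDF has no counterpart in controls.
- Exceeding a fixed level such as the entry limit of 6.3 log10 IU/mL: controls met this at enrolment.

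The protocol does not choose among them.

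**Does the mixed model supply the comparison?** It uses the 24-week baseline and asks whether levels change differently with and without TDF. Neither set of named contrasts is a between-arm comparison at 28 weeks postpartum, and an overall test of differing change would not isolate that visit. Fisher's test is therefore the only analysis assigned to this comparison.

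**Figures in the plan.** None belongs to this outcome. The 35 per group is for transmission, 30% against 5%. With two-sided 0.05 and 80% power (power is not stated, so this is assumed), n = [1.96√(2 × 0.175 × 0.825) + 0.842√(0.30 × 0.70 + 0.05 × 0.95)]² / 0.25² = 35.06. This agrees with the stated 35 (36 if rounded up) and does not depend on the present point.

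**How much could the cut-point matter?** The protocol gives no SD or expected difference at 28 weeks, so this is only an illustration. The 60 per arm comes from the Randomization item. Normal log10 values, a true shift of 0.5 SD and two-sided 0.05 are assumed.
- Comparing levels: power = Φ(0.5 × √(60/2) − 1.96) = Φ(2.739 − 1.960) = Φ(0.779) ≈ 78%.
- Fisher's test with a cut-point c SD above the lower arm's mean: the proportions above it are 1 − Φ(c) and 1 − Φ(c − 0.5). Power is the summed binomial probability of all tables with p < 0.05.

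| c | Lower arm | Other arm | Fisher power |
|---|---|---|---|
| 0.25 (midway) | 40.1% | 59.9% | 53% |
| 1.0 | 15.9% | 30.9% | 41% |
| 1.5 | 6.7% | 15.9% | 25% |
| 2.0 | 2.3% | 6.7% | 7% |
| −1.0 | 84.1% | 93.3% | 25% |
| −1.5 | 93.3% | 97.7% | 7% |

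The same data can thus give anything from a moderately powered to an almost powerless test, according to a number that the plan does not state.

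**The case against.** The strongest defence is that a proportion recovered may be meant. Recovery shares its sentence with the transmission rate, and the Abstract's footnote says that the English text translates only key points. Fisher's test would be valid for a predefined binary recovery, and controls could serve as the reference at the same time point. A cut-point could also sit in a statistical analysis plan that is not shown. All of this is fair, and it means that a cut-point chosen after seeing the data is a risk and not an established fact. It does not rescue the text, which names levels, gives no category and anchors recovery to an event absent in one arm.

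A reader might also infer more than the protocol supports:
- That this is the trial's only secondary outcome. It is the one in the outcomes item; the Abstract labels others.
- That controls have never been treated. Only HBV treatment within 6 months is excluded, so the protocol supports no more than that they receive no TDF in the trial.
- That the 24-week value goes unused. The mixed model uses it; only the 28-week Fisher comparison does not.
- That a non-significant Fisher result would be reported as recovery. The protocol states only a 0.05 rule for significance.

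**Conclusion.** Wrong as written, and it should be fixed. The protocol assigns a test for categories to an outcome described as a level, defines no category, and leaves recovery without meaning in the control arm. The mixed model limits the damage but contains no named contrast that replaces the Fisher comparison.

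The size cannot be taken from the documents. The range of 7% to 53% against 78% rests on an assumed shift of 0.5 SD, normality and 60 women per arm with a 28-week value. It shows how far the choice of cut-point matters and is not an estimate of this trial's loss.

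It would be tempting to treat this as a threat to the trial's main conclusion. The documents do not support that: the primary outcome is binary, Fisher's test suits it, and the sample size rests on it alone. The differing lists of secondary outcomes in the Abstract and the outcomes item are a minor matter of consistency.

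**What to change.** - Define the secondary outcome as maternal log10 HBV DNA (IU/mL) at 28 weeks postpartum.
- Compare the arms by a 28-week between-arm contrast in the mixed model, or by ANCOVA, in either case adjusted for the 24-week log10 value. Report the mean difference with its 95% CI. The precision gained by adjustment depends on a correlation that the protocol does not give.
- Keep Fisher's test for the transmission rate. If a binary recovery is also wanted, fix its reference and threshold, meaningful in both arms, before the data are seen.
- Treat any change from 24 weeks of gestation to 28 weeks postpartum within the TDF arm as descriptive only. Women are enrolled because their HBV DNA lies above a threshold, so regression to the mean applies.
- Make the Abstract and the outcomes item list the same secondary outcomes.

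The cost is protocol wording. The Intervention section already schedules blood before TDF and up to 28 weeks postpartum in both arms, so no new sample is needed. Women excluded for preterm delivery or loss to follow-up under Study Design may still lack a 28-week value, and this change does not solve that.

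### The HBV DNA contrasts named for testing are within-arm as worded, so none gives the TDF-minus-control difference at delivery

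*Protocol*

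**What the plan says.** The Statistical Analysis section of the protocol states the question in between-arm terms: a mixed model will "analyze if the serum HBV DNA levels change differently with or without TDF treatment". The next sentence names the planned contrasts. The first is "change in HBV DNA for each group between baseline and delivery time". The second is "differences from weeks to the weeks", which the text places "within TDF treatment group". The threshold for all tests is "The p value less than 0.05 will be considered as statistically significant". Transmission and HBV DNA recovery 28 weeks after delivery "between the two groups will be compared by Fisher exact tests".

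Other sections bear on how these contrasts read:

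- **Study Objectives, item 2:** to "monitor the effect of TDF on the dynamic changes of HBV DNA levels in the pregnancy".
- **Abstract:** marks maternal HBV DNA monitored during pregnancy as a secondary outcome. Outcomes measurement (Study Procedures) defines the secondary outcome only as recovery at 28 weeks postpartum.
- **Study Design, inclusion criteria:** serum HBV DNA of at least 6.3 log10 IU/mL.
- **Study Procedures, screening:** "According to the parameters of pregnancies at 24 weeks of gestation, the pregnant women will be enrolled or not for the study".
- **Intervention:** both arms are sampled before TDF would start, then 4-weekly to delivery and on to 28 weeks postpartum. TDF runs from enrolment at 24 weeks of gestation to 4 weeks postpartum.

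**The concern.** The question and the named contrasts do not match. The question is whether the arms differ in their change. The contrasts ask whether each arm changed, and whether the TDF arm changed from visit to visit. Neither, as worded, returns the quantity that randomisation was set up to estimate, namely how much lower HBV DNA is at delivery because of TDF.

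The number at stake is the antenatal effect size for objective 2. A within-arm fall mixes any drug effect with whatever else moves HBV DNA after 24 weeks, including regression to the mean if women qualify on a threshold at about the visit that serves as baseline. The Fisher test of postpartum recovery is between arms, but it concerns a time well after TDF has stopped and does not fill the gap at delivery.

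**Working it through.** The protocol gives no planning figure for HBV DNA, so there is none to reproduce on this point. Its sample size (35 per group) concerns transmission and plays no part here.

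**1. What each planned quantity estimates.** Let τ be the effect of TDF on the change in log10 HBV DNA from 24 weeks to delivery. Let δ be everything shared by the arms: regression to the mean, drift in pregnancy, assay variation over time.

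- TDF arm, baseline to delivery: expected change = τ + δ
- Control arm, baseline to delivery: expected change = δ
- TDF arm, week to week: the same mixture for each interval
- TDF minus control: (τ + δ) − δ = τ

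Only the last line isolates τ, and it is not among the named contrasts.

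**2. Why δ need not be zero.** Enrolment requires at least 6.3 log10 IU/mL and is decided on the 24-week parameters. TDF starts on enrolment, with a sample taken beforehand. If the qualifying value is also the baseline, then under a stable mean and variance the expected fall at a later visit is (1 − ρ) × (mean of those selected − mean of the population screened), where ρ is the correlation between visits. With an assumed ρ of 0.7 the fall is 0.3 of that distance. The protocol gives neither ρ nor the distribution of HBV DNA, so the size in log10 units cannot be stated.

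**3. What the overall group-by-time test covers.** Assume delivery near 40 weeks.

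- Antenatal samples: 24, 28, 32, 36 and about 40 weeks = 5
- Postpartum samples: 28 ÷ 4 = 7
- Total: 5 + 7 = 12
- Group-by-time degrees of freedom, with visit as a category: (12 − 1) × (2 − 1) = 11
- Post-baseline samples up to the end of TDF (28, 32, 36, about 40 weeks, and 4 weeks postpartum): 5
- Post-baseline samples after TDF has stopped (8 to 28 weeks postpartum): 6

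The section does not say which visits enter the model. If all do, a significant result says that the arms' courses differ somewhere. It does not say by how much at delivery, and more than half of the post-baseline points are off drug. If only visits to delivery enter, the mixing disappears but the test still has 5 − 1 = 4 degrees of freedom and yields no single effect size.

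**4. What is lost if within-arm results stand in for the comparison.** This is an illustration, since the protocol states no such rule. Under no treatment effect, with 60 per arm:

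| Situation | Exactly one arm significant | Direct between-arm test significant |
|---|---|---|
| No time trend (simulated, ρ = 0.7) | about 9% | 4.3% to 4.8% |
| Shared trend that each arm detects with about 51% power (simulated) | about 50% | 4.9% |

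Arithmetic agrees: 2 × 0.05 × 0.95 = 0.095, and 2 × 0.515 × 0.485 = 0.50. The direct contrast holds its level in both situations.

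**The case against.** The strongest reply is that a between-arm test is already planned, because the mixed model is there to compare the course of HBV DNA with and without TDF. This stands. A reader might infer that objective 2 ignores the control arm, and the document does not support that. The gap is narrower: no between-arm contrast at delivery is named.

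A reader might also infer from the unadjusted 0.05 threshold that the trial does not keep its 5% level. The document does not support that either. There is one primary outcome with one between-group Fisher test, and supportive HBV DNA contrasts add nothing to its error rate. The protocol claims no familywise control over them, does not fix how many week-to-week tests there will be, and may leave multiplicity to an SAP that is not shown.

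The protocol nowhere says that an effect will be read from significance in one arm and not in the other, so the last step of the working shows a hazard and not a planned rule. Regression to the mean is expected to be equal in randomised arms and does not bias the group-by-time test. The small study cited in the Introduction reported falls of 2 to 4 log10 copies/mL within 4 weeks on TDF. If that holds here, the direction of the effect is unlikely to be misjudged.

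Finally, the text is a translation of key points, and the first contrast may have been meant as a comparison of changes between groups. If so, the wording should say it. None of these replies supplies the missing estimate.

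**Conclusion.** The point holds in a limited form. As worded, both named contrasts are within-arm and neither estimates the randomised effect of TDF on HBV DNA at delivery, although the Abstract treats antenatal HBV DNA as a secondary outcome and objective 2 asks about it. The planned group-by-time test is a valid between-arm test but gives no effect size, and it spans on-drug and off-drug periods if all visits enter.

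Three assumptions carry the detail: delivery near 40 weeks for the visit count, all visits entering the model for the on-drug and off-drug mixing, and the 24-week qualifying value serving as baseline for regression to the mean. The amount of regression to the mean cannot be derived from the document. The core mismatch between question and contrasts needs none of these assumptions. The primary analysis of transmission is untouched, so this is an inexpensive improvement to a supportive analysis and not a threat to the trial's main conclusion.

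**What to change.** In the Statistical Analysis section, replace the named contrasts with one: the TDF-minus-control difference in change of log10 HBV DNA from the 24-week pre-treatment sample to the last sample before delivery, estimated from the same mixed model with baseline log10 HBV DNA taken into account, with a 95% CI. State which visits enter the model. Report the within-arm and week-to-week changes descriptively, as estimates and plots.

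The cost is a few sentences. Both arms are already sampled on the same schedule, so no extra visits, samples or participants are needed and the model is unchanged.
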